### Two years assessments

All surviving children will be formally assessed at two years of age, corrected for prematurity, by a developmental paediatrician and psychologist or other trained assessor who can administer the Bayley Scales, all of whom remain blinded to treatment group assignment. The parents will be contacted by the follow-up coordinator at the recruitment hospital to organise this appointment. However, if the family does not live close to this hospital, a member of the study team at the coordinating centre will telephone them to discuss a suitable alternative. Assessments will be made of health, neurodevelopment, behaviour, growth and blood pressure.

#### Motor function

The paediatric assessment will include a neurological examination to diagnose cerebral palsy (loss of motor function and abnormalities of muscle tone and power) and other disability outcomes according to previously reported criteria [37]. The severity of gross motor function in children will be classified using the Gross Motor Function Classification System (GMFCS) [38].

#### Psychological assessments

The psychological assessment will include the cognitive, motor and language scales of the Third Edition of the Bayley Scales of Infant Development (BSID-III) [39]. This is well-standardised with demonstrated validity and reliability. Psychological test scores will be recorded as a standardised normal score [derived from test score - mean/standard deviation (SD)]. Children with severe developmental delay who are unable to complete the psychological assessment will be given a standardised score of - 4 SD.

#### Behaviour

The child’s caregiver will be asked to complete the Child Behaviour Checklist [40].

##### General health, health resource utilisation, blood pressure, body size, and quality of life

A general history and physical examination will determine the presence of any significant chronic illness, and data regarding hospital readmissions will be confirmed, where necessary, from the admitting hospital or doctor. Children will be considered blind if visual acuity in both eyes is worse than 6/60. Children will be considered deaf if their hearing loss is sufficient to require hearing aid(s), or worse. Blood pressure will be measured and converted to Z-scores relative to American data for blood pressure for age, height and gender in childhood [41].

Questionnaires will be completed by the child’s caregiver about any respiratory morbidity, history of illness or injury and use of health services since primary hospitalisation.

The child’s height, weight, and head circumference will be measured in the standard way, and values for the relevant centile, percent of median, and standard deviation scores (Z scores) specific for age and gender will be computed from the British Growth Reference [42].

### Categorisation of neurosensory disability

Children will be considered to have a neurosensory impairment if they have cerebral palsy, blindness, deafness or any of the Bayley Scale scores more than 1 SD below the mean (<−1 SD). The neurosensory disabilities imposed by the various neurosensory impairments will be classified as severe, moderate or mild [37] (Table 1).

**Table 1 T1:** **Neurosensory disability classifications**[37]

**Severe disability**	Any severe cerebral palsy (child non-ambulant and likely to remain so; GMFCS level 4 or 5), severe developmental delay (standardised score <−3 SD) or blindness.
**Moderate disability**	Moderate cerebral palsy (child non-ambulant at 2 years of age but who is likely to ambulate subsequently; GMFCS level 2 or 3), or deafness, or moderate developmental delay (standardised score from −3 SD to <−2 SD).
**Mild disability**	Mild cerebral palsy (child walking at 2 years of age with only minimal limitation of movement (GMFCS level 1), or suspect developmental delay (standardised score from −2 SD to <−1 SD).
**No neurosensory disability**	Children without any neurosensory impairment.

### Primary study endpoints

The primary study endpoint measured in the children at two years’ corrected age is the incidence of death or any neurosensory disability defined as stillbirths, deaths from live born infants before hospital discharge and deaths after hospital discharge; and any neurosensory disabilities that include the neurosensory impairments of cerebral palsy, blindness, deafness and any developmental delay defined as a standardised score more than 1 SD below the mean (<−1 SD).

### Secondary study endpoints

#### For the infant/child

•Death or major neurosensory disability (with major neurosensory disability defined as severe and moderate disability and includes blindness, deafness, cerebral palsy in a child non-ambulant by two years of age or a standardised score <−2 SD).

•Individual components and severity of the primary outcome (death, cerebral palsy, blindness, deafness, developmental delay).

•Neonatal outcomes measured prior to primary hospital discharge, including IVH, severe IVH (Grade 3 or 4), periventricular leukomalacia, retinopathy of prematurity needing treatment, patent ductus arteriosus needing treatment, respiratory distress syndrome, severity of any neonatal lung disease, chronic lung disease (need for oxygen at 36 weeks post-menstrual age or 28 days of life if born after 32 weeks gestation), use of mechanical ventilation, confirmed infection within the first 48 hours, infection after the first 48 hours, proven necrotising enterocolitis, body size at birth (weight, length and head circumference) and at discharge home after birth.

•Childhood outcomes assessed at two years’ corrected age including body size and corresponding Z scores, general health of the child (including use of health services since primary hospitalisation), childhood respiratory morbidity, blood pressure Z scores and proportions in hypertensive ranges and behaviour as assessed by the Child Behaviour Checklist [40].

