## Background

Children born preterm have a higher than average risk of dying in the first weeks of life and survivors experience higher rates of neurosensory disability than children born at term [1,2]. There is clear evidence that antenatal corticosteroids, both dexamethasone and betamethasone, given to women at risk of preterm birth substantially improve short-term neonatal health, increase the chance of the baby being discharged home alive, and reduce childhood neurosensory disability, remaining safe into adulthood [3]. The type of antenatal corticosteroid to use in clinical practice remains unclear [3]. Dexamethasone and betamethasone are both recommended [4] and widely used [1].

Is dexamethasone better than betamethasone, or vice versa? Our meta-analysis, using the limited data available from randomised trials that have directly compared the two treatments shows that dexamethasone reduces the risk of the baby developing intraventricular haemorrhage (IVH) to a greater extent than betamethasone [5]. While reduced IVH is a very important outcome, achieving a reduction in long-term survival free of any disability is the most important goal [2]. Data regarding the effects on long-term health are sparse.

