#### Analysis and reporting of results

Data will be analysed by a statistician independent of the clinical investigators. Potential confounding variables will comprise sociodemographic variables, such as ethnicity, language spoken at home, family structure, mother’s marital status, social class, and mother’s and father’s education, as well as gender. Comparisons will be made between treatment groups for the primary and secondary endpoints using an intention to treat approach. Analyses will make adjustments for the stratification variables and for important baseline predictors including gestational age at trial entry, and reasons for risk of preterm birth. Unadjusted analyses will also be performed. Log binomial regression and linear regression will be used to examine dichotomous and continuous outcomes respectively, with results presented as relative risks or differences in means along with 95% confidence intervals. Adjustment will be made for clustering due to multiple births for infant outcomes using generalised estimating equations. *P*-values < 0.05 will be considered statistically significant.

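### Chronic lung disease can be observed only in babies alive at 36 weeks' post-menstrual age (or 28 days), so a difference in early deaths could modestly tilt this secondary comparison; a death-or-chronic-lung-disease endpoint should be added beside it

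*Protocol article*

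**What the plan says.** Under Secondary study endpoints, For the infant/child, the protocol article gives a list headed "Neonatal outcomes measured prior to primary hospital discharge". One item is "chronic lung disease (need for oxygen at 36 weeks post-menstrual age or 28 days of life if born after 32 weeks gestation"). It is not combined with death.

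Death is handled in two ways elsewhere:

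- It is combined with neurosensory disability in the primary endpoint, "death or any neurosensory disability defined as stillbirths, deaths from live born infants before hospital discharge and deaths after hospital discharge", and in the secondary endpoint "Death or major neurosensory disability".
- It is a secondary endpoint in its own right, through "Individual components and severity of the primary outcome (death, cerebral palsy, blindness, deafness, developmental delay").

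Under Analysis and reporting of results: "Comparisons will be made between treatment groups for the primary and secondary endpoints using an intention to treat approach". Dichotomous outcomes are analysed by log binomial regression and reported as relative risks. The article does not say how a death before the lung assessment enters that comparison.

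**The concern.** Oxygen need at a fixed time can be recorded only in a baby who is alive then. For a birth before 28 weeks, the 36-week assessment falls more than 8 weeks after birth (36 − 28 = 8). The Background says that "Children born preterm have a higher than average risk of dying in the first weeks of life", which lies within that wait.

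A baby who dies first must be treated in one of two ways:

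- With all infants in the denominator, the baby counts as free of chronic lung disease.
- With survivors only, the baby leaves the comparison, and the arms are compared on groups selected after randomisation.

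Either way, if one drug keeps alive fragile babies who would have died on the other, some of them will need oxygen at 36 weeks and will raise that drug's rate of chronic lung disease. The comparison could then point the opposite way to the net effect on death and lung disease together. This applies equally to whichever drug has fewer early deaths.

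The plan already avoids this problem for disability by combining it with death. Neonatal morbidity is also one of its stated secondary hypotheses.

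**Working it through.** **The plan's own figures.** The article gives no figure for chronic lung disease. The sample size is needed for the chance calculations, so it was checked first. For 27.0% v 20.1% (two-sided 0.05, 80% power, 1:1 allocation assumed, pooled variance, no continuity correction) the number is 593 per arm, and 2 × 593 × 1.2 / 0.95 = 1498. For 27.0% v 34.5% it is 594 per arm, giving 1501. Both agree with the 1499 in the Sample size section, which is used here. The 1449 in the Abstract does not reproduce.

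**Inputs**

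| Input | Value | Source |
|---|---|---|
| d0, deaths with betamethasone | 6.05% up to two years | Sample size section |
| r, relative reduction in death with dexamethasone | 10% to 50%, middle 25% | assumed |
| b, chronic lung disease among betamethasone survivors | 5% to 15%, middle 10% | assumed |
| s, chronic lung disease among the babies saved | 40% to 80%, middle 60% | assumed |

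Two further assumptions: neither drug changes chronic lung disease in babies who would survive on both, and all 6.05% of deaths precede the assessment. The second is an upper bound, because the figure runs to two years.

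**Formulae**

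- Deaths with dexamethasone: d1 = d0(1 − r)
- Chronic lung disease per infant: c0 = (1 − d0)b and c1 = c0 + (d0 − d1)s
- RR, all infants: c1/c0
- RR, survivors: [c1/(1 − d1)]/b
- RR, death or chronic lung disease: (d1 + c1)/(d0 + c0)

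**Middle case**

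- d1 = 0.0605 × 0.75 = 0.0454, so 0.0151 are saved.
- c0 = 0.9395 × 0.10 = 0.0940; c1 = 0.0940 + 0.0151 × 0.60 = 0.1030.
- All infants: 9.4% v 10.3%, RR 1.10.
- Survivors: 0.1030/0.9546 = 10.8% v 10.0%, RR 1.08.
- Death or chronic lung disease: 0.0605 + 0.0940 = 15.4% v 0.0454 + 0.1030 = 14.8%, RR 0.96.

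**Across the assumed ranges**

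| Comparison | RR, dexamethasone v betamethasone |
|---|---|
| Chronic lung disease, survivors | 1.01 to 1.47 |
| Chronic lung disease, all infants | 1.02 to 1.52 |
| Death or chronic lung disease | 0.83 to 0.99 |

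**Conditions for the tilt.** With all infants in the denominator, any s > 0 is enough once deaths fall. With survivors only, s must exceed b: the babies saved must have more lung disease than other survivors. The composite improves whenever s < 1.

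**If only half the deaths come first.** Middle case with d0 = 0.03025: d1 = 0.0227, c0 = 0.96975 × 0.10 = 0.0970, c1 = 0.0970 + 0.0076 × 0.60 = 0.1015. Survivors: 0.1015/0.9773 = 10.4% v 10.0%, RR 1.04. Composite: 12.7% v 12.4%, RR 0.98.

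**Chance of a significant spurious excess.** The effective number per arm is m = 1499/2/1.2 = 624.6. With p̄ the mean of p0 and p1, the chance is Φ{[(p1 − p0) − 1.96√(2p̄(1 − p̄)/m)] / √(p0(1 − p0)/m + p1(1 − p1)/m)}.

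- Middle case, survivors, 10.0% v 10.8%: (0.0079 − 0.0339)/0.0173 = −1.50, about 7%. The nominal rate in that direction is 2.5%.
- Most extreme case (b 5%, r 50%, s 80%), 5.0% v 7.3%: about 40%.

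**A second illustration, all rates assumed.** Deaths before assessment are 5% v 3%, chronic lung disease is 12% among betamethasone survivors, and half of the extra survivors need oxygen.

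- All infants: 0.95 × 0.12 = 11.4% v 11.4% + 0.02 × 0.5 = 12.4%, RR 1.09.
- Survivors: 12.0% v 0.124/0.97 = 12.8%, RR 1.07.
- Composite: 16.4% v 15.4%, RR 0.94.

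The 1.0-point excess has a standard error of about 1.8 points, so it is about 0.55 standard errors, with about an 8% chance of significance.

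**The case against.** The definition is clear and timed, and nothing in the article contradicts it. Denominators and the handling of earlier deaths are commonly left to a full protocol or analysis plan, neither of which is shown. The neonatal list is also introduced as non-exhaustive, so a composite may exist elsewhere. This stands: the article contains no error on this point, and silence about denominators is not the finding. What the article does fix is a lung endpoint listed without death, and neither choice of denominator removes the tilt.

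Death is already a secondary endpoint, so a reader could set it beside chronic lung disease. This also stands as mitigation. It is incomplete, because that endpoint also counts stillbirths and deaths after discharge, and two separate rows do not give the net effect.

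A reader might infer that the trial is designed to detect a difference in early mortality, and hence that the bias is to be expected. The documents do not support this. The trial is powered for death or disability combined. At m = 624.6 per arm, power for an assumed 5% v 3% mortality is only about 44% (Φ[(0.0200 − 0.0217)/0.0111] = Φ(−0.16)). The Background also reports no significant difference in death in the earlier head-to-head trials.

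A reader might also infer that many of the deaths precede the assessment. The article says only that risk is raised in the first weeks and gives no split by time.

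Other endpoints, such as treated retinopathy, infection after 48 hours and body size at discharge, are also cut short by death, so chronic lung disease is not unique. It is the named neonatal endpoint with the latest fixed assessment time.

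**Conclusion.** The point holds as an optional improvement to a secondary endpoint. If early mortality differs, the stand-alone chronic lung disease comparison can be tilted against the drug with fewer deaths. The problem lies mainly in the 36-week branch; 28 days after a birth beyond 32 weeks should compete with few deaths.

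The likely size is modest: a relative risk of about 1.08 among survivors in the middle case, with about a 7% chance of a significant spurious excess. Chances near 40% need the most extreme assumptions. Only the 6.05% mortality comes from the article. The mortality difference, the lung disease rates and the timing of deaths are assumptions. The primary endpoint is unaffected.

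The stronger conclusion, that chronic lung disease is a faulty endpoint to be replaced by the composite, does not follow. The lung-specific outcome has its own value, and a composite can hide a lung effect when mortality moves the other way.

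**What to change.** Under Secondary study endpoints, For the infant/child, keep chronic lung disease as listed and add one endpoint: *death before 36 weeks' post-menstrual age (28 days if born after 32 weeks) or chronic lung disease at that time, among all infants*. Show death before that time and chronic lung disease separately beneath it. State whether stillbirths count as deaths here, as they do in the primary endpoint.

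Confirm that date of death is recorded. Collection from case notes makes this likely, but the article names only stillbirths and deaths before and after discharge. Those categories cannot separate an in-hospital death before 36 weeks from a later one.

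The cost is one definition and one block in a table, with no new data if dates of death are held. The downside is one more secondary endpoint, and one less specific to the lung, which is why the components stay visible.

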#### For the mother

•Maternal perinatal infectious morbidity (defined as clinical chorioamnionitis requiring intrapartum antibiotics and/or use of postpartum antibiotics).

#### Sample size

With a predicted mortality rate of 6.05% up to two years and a predicted rate of neurosensory disability in survivors of 20.9%, we estimate the rate of our primary outcome of death or neurosensory disability at two years corrected age in an Australian/New Zealand population exposed antenatally to betamethasone to be 27.0% [3,37,43,44].

A trial of 1499 children, allowing 5% loss to follow up and with a design effect of 1.2 to allow for the clustering of babies within mothers, will have 80% power to detect a statistically significant difference at an alpha level of 0.05 (two-tailed) of either:

•a decrease in the combined outcome of death or neurosensory disability from 27.0% to 20.1% (Absolute Risk Difference (ARD) 6.9%; Relative Risk Difference (RRD) 25.6%) with dexamethasone compared with betamethasone, or;

•an increase from 27.0% to 34.5% (ARD 7.5%; RRD 27.8%).

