**Methods/Design:**

*Design* randomised, multicentre, placebo controlled trial.

*Inclusion criteria* women at risk of preterm birth at less than 34 weeks’ gestation with a singleton or twin pregnancy and no contraindications to the use of antenatal corticosteroids and who give informed consent.

*Trial entry & randomisation* at telephone randomisation eligible women will be randomly allocated to either the dexamethasone group or the betamethasone group, allocated a study number and corresponding treatment pack.

*Study groups* women in the dexamethasone group will be administered two syringes of 12 mg dexamethasone (dexamethasone sodium phosphate) and women in the betamethasone group will be administered two syringes of 11.4 mg betamethasone (Celestone Chronodose). Both study groups consist of intramuscular treatments 24 hours apart.

*Primary study outcome* death or any neurosensory disability measured in children at two years’ corrected age.

*Sample size* a sample size of 1449 children is required to detect either a decrease in death or any neurosensory disability from 27.0% to 20.1% with dexamethasone compared with betamethasone, or an increase from 27.0% to 34.5% (two-sided alpha 0.05, 80% power, 5% loss to follow up, design effect 1.2).

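### The 27.0% control rate is the plain sum of mortality and a disability rate stated for survivors only; those inputs give 25.7%, so rate and wording must be reconciled

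*Protocol article*

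**What the plan says.** The Sample size section of the protocol article builds its control rate from two components: "With a predicted mortality rate of 6.05% up to two years and a predicted rate of neurosensory disability in survivors of 20.9" per cent. From these it estimates the rate of the primary outcome "in an Australian/New Zealand population exposed antenatally to betamethasone to be 27.0" per cent.

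The Primary study endpoints section defines that outcome over all children. It is "the incidence of death or any neurosensory disability defined as stillbirths, deaths from live born infants before hospital discharge and deaths after hospital discharge", together with any neurosensory disability.

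The design effects start from the 27.0%. The first is "a decrease in the combined outcome of death or neurosensory disability from 27.0% to 20.1" per cent (absolute difference 6.9 points, relative difference 25.6%). The second is an increase from 27.0% to 34.5% (7.5 points, 27.8%). The Sample size section gives 1499 children for 80% power at two-sided alpha 0.05, with 5% loss to follow-up and a design effect of 1.2. The abstract repeats the same control rate, "from 27.0% to 20.1% with dexamethasone compared with betamethasone".

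**The concern.** Two rates can be added to give a composite only if they share a denominator and do not overlap. As worded, these two do not share a denominator: mortality is a share of all children, disability a share of those who survive. Adding them counts the disability rate as if it also applied to the children who died.

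The control rate is the starting point for both target rates, both absolute and both relative differences, and the claim of 80% power. If it is too high, the effects that 1499 children can detect are misdescribed. The relative scale is relevant because the section on analysis and reporting of results plans log binomial regression with relative risks as the reported effect for dichotomous outcomes.

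**Working it through.** **Inputs (Sample size section).** Mortality 6.05%; disability 20.9%, described as *in survivors*; stated composite 27.0%; targets 20.1% and 34.5%; two-sided alpha 0.05; power 80%; loss 5%; design effect 1.2; 1499 children. No allocation ratio is stated; 1:1 is assumed.

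**Step 1: reproduce the plan's sample size.** Pooled-variance formula for two proportions, no continuity correction:

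n per arm = [1.96 × √(2p̄(1 − p̄)) + 0.8416 × √(p₁(1 − p₁) + p₂(1 − p₂))]² / (p₁ − p₂)², with p̄ = (p₁ + p₂)/2.

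- 27.0% vs 20.1%: 593 per arm; 1186 × 1.2 = 1423.2; / 0.95 = 1499 after rounding up.
- 27.0% vs 34.5%: 594 per arm; 1188 × 1.2 = 1425.6; / 0.95 = 1501.

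The decrease reproduces 1499 exactly, which supports the 1:1 assumption. The effective number per arm at 1499 is 1499 × 0.95 / 1.2 / 2 = 593.4. Power with that number is 80.1% for the decrease and 80.0% for the increase.

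**Step 2: reproduce the control rate.**

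- Plain sum: 6.05% + 20.9% = 26.95%, which rounds to 27.0%.
- Weighted by survival: 0.0605 + (1 − 0.0605) × 0.209 = 0.0605 + 0.1964 = 0.2569, or 25.7%.

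The gap is 27.0 − 25.7 = 1.3 points, too large for rounding. For 27.0% to follow from 6.05% mortality, disability among survivors would have to be (27.0 − 6.05) / 93.95 = 22.3%.

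**Step 3: power at 1499 children if the control rate is 25.7%** (same formula, 593.4 per arm).

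| Effect held fixed | Rates | Power | Children for 80% |
|---|---|---|---|
| Relative decrease 25.6% | 25.7% to 19.1% | 77.5% | about 1600 |
| Relative increase 27.8% | 25.7% to 32.8% | 77.1% | about 1610 |
| Absolute decrease 6.9 points | 25.7% to 18.8% | 81.6% | 1438 |
| Absolute increase 7.5 points | 25.7% to 33.2% | 81.0% | 1463 |

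**Step 4: what 1499 children detect at 80% power from 25.7%.** Solving the same formula for the second rate:

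- decrease to 18.9%: 6.8 points, relative difference 26.3%;
- increase to 33.1%: 7.4 points, relative difference 28.8%.

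**The case against.** Four points can be made for the plan.

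1. *The wording may be loose rather than the sum wrong.* If 20.9% is really the share of all children who survive with a disability, then 27.0% is right and only the words *in survivors* are at fault. The rates are credited to cited sources that are not at hand, and nothing else in the article settles the matter. This stands: a reader might conclude that 25.7% is the proven control rate, and the document does not support that. It shows only that inputs and result cannot both be right as written.

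2. *The loss of power depends on the scale.* Each effect is given as a pair of rates with both an absolute and a relative difference, and neither is named as the design target. Holding the absolute differences costs no power. This stands too. It limits the shortfall to the relative effects.

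3. *The sample-size calculation is sound.* Given 27.0% and 20.1%, 1499 reproduces exactly. Agreed: only one input is in question.

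4. *The trial is not seriously underpowered.* A reader might set 25.7% against the unchanged 20.1% and infer a large loss of power. That comparison tests a difference of 5.6 points, smaller in both absolute and relative terms than anything the plan claimed to detect, so it does not measure the harm.

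The abstract's figure of 1449 children, against 1499 in the Sample size section, is a separate discrepancy and adds nothing here.

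None of this removes the contradiction between the stated inputs and the stated composite.

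**Conclusion.** The point holds as an internal inconsistency with a modest consequence. Read literally, the control rate is overstated by 1.3 percentage points, and the claim of 80% power fails by 2.5 to 2.9 points for the stated relative effects while holding for the stated absolute differences. At 80% power the smallest detectable relative differences move from 25.6% to 26.3% (decrease) and from 27.8% to 28.8% (increase).

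These figures assume that the words *in survivors* are meant literally, 1:1 allocation, a pooled-variance test without continuity correction, and the plan's own design effect and loss. If 20.9% refers to all children, the stated power is unaffected and the fault is one of wording. The finding does not call for a larger trial and does not affect the endpoint or the analysis.

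**What to change.** First check the 20.9% against the source from which it was taken.

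- **If it is a rate among survivors:** replace 27.0% with 25.7% in the Sample size section and in the abstract. Then either restate what 1499 children detect at 80% power, using the two pairs from step 4 of the working, or keep the present relative effects and state power as about 77%. Recalculate the target rates and the absolute and relative differences to match.
- **If it is a share of all children:** keep 27.0% and all figures that follow from it, and correct the words *in survivors*. The rate among survivors would then be 20.9 / 93.95 = 22.2%.

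In either case, state the formula that combines the two components and the allocation ratio. The cost is one check of the source and a few restated figures or words. In the first case the stated relative effects become slightly less favourable. No extra patients are needed.
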